### Outcomes

Baseline evaluations (T0) will be conducted within 7 days before the initiation of the intervention. Post-intervention evaluations (T1) will be conducted within 7 days after the final intervention session.

The primary outcome will be the change in gait speed from T0 to T1. Gait speed will be measured as the average value from two trials of the 10-meter walk test. This test is sensitive to mobility impairment, predicts disability and falls, and is feasible for use in clinical settings, demonstrating both reliability and validity (37, 38).

The secondary outcomes will be the change from T0 to T1 of the following assessments: 4-meter walk test, TUG, Short Physical Performance Battery (SPPB), BBS, MDS-UPDRS, Freezing of Gait Questionnaire (FoGQ), gait parameters measured by an IMU sensor-based gait analysis system (Human Track, R. Biotech Co. Ltd., Seoul, Korea) (39) and the GAITRITE system (CIR Systems, PA, United States) (40), muscle strength and endurance measured by isokinetic dynamometer Biodex system (Biodex System 4, Biodex Medical Systems, Shirley, NY, United States) (41), thickness of quadriceps muscles measured by ultrasound, body composition measured by Dual-energy X-ray absorptiometry (DEXA) (42), cognitive function measured by Mini-Mental State Examination (MMSE), and depression measured by Beck Depression Inventory (BDI). In addition, questionnaires assessing comfort and usability, along with participants’ feedback, will be collected after the completion of the intervention sessions.

The TUG evaluates gait, balance, and fall risk. Participants will rise from a chair, walk 3 meters to a cone, turn, return to the chair, and sit down. Completion time (seconds) will be recorded (43). The SPPB will assess balance, walking ability, and transfers. Each component is scored on a 0–4 scale, with a total score ranging from 0 to 12, where higher scores indicate better performance. The BBS assesses functional standing balance through 14 tasks of increasing difficulty, including sitting, standing, single-leg stance, and positional changes. Each item is scored on a 0–4 scale, with a maximum total score of 56, where higher scores indicate better balance ability (44).

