The MDS-UPDRS is a comprehensive tool for evaluating Parkinson’s disease across four domains: (I) non-motor experiences of daily living, (II) motor experiences of daily living, (III) motor examination, and (IV) motor complications. Parts I and II are based on patient or caregiver questionnaires, while Parts III and IV are assessed by a clinician. Each item is rated on a 0–4 scale, with higher scores indicating greater impairment, allowing for a detailed assessment of both motor and non-motor symptoms (45). The FoGQ is a brief, reliable self-reported instrument designed to assess FoG in individuals with Parkinson’s disease. It consists of six items evaluating the frequency, duration, and impact of FoG episodes, such as start hesitation and turning hesitation. Each item is scored on a 0–4 scale, with higher scores indicating more severe symptoms (46).

The gait parameters measured by the IMU sensor-based gait analysis system and the GAIRRite system will include stride length, step length, cadence, proportion of single and double support, proportion of swing and stance phases, and the range of motion (ROM) of hip, knee, and ankle joint angles. The parameters measured by the Biodex system will include the number of repetitions, peak torque (N·m), peak torque/body weight (%), maximal repetition total work (J), coefficient of variation (CV, %), average power (W), and total work (J). Measurement will be obtained for both knee flexion and extension at angular velocities of 60°/second and 180°/second.

Quadriceps muscle thickness will be measured by ultrasound. A single trained investigator will perform all measurements. The probe will be placed transversely, 10 cm above the superior border of the patella, along the line from the anterior superior iliac spine to the patella (47, 48). Body composition will be assessed using DEXA, including measurements of body mass index (BMI), skeletal muscle mass index (SMI), total body fat percentage, fat mass index, and bone mineral density (BMD).

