### Statistical methods

Demographic and clinical characteristics will be summarized using frequencies and percentages for categorical variables and means with standard deviations (SD) for continuous variables. The Shapiro–Wilk test will be used to assess the normality of continuous variables. To compare baseline characteristics between the intervention and control groups, an independent t-test will be applied for normally distributed variables, while the Mann–Whitney U test will be used for non-normally distributed variables.

All participants who undergo the intervention will be included in the intention-to-treat (ITT) population, which will also serve as the basis for safety analyses. Participants in the ITT population who complete both baseline and post-intervention assessments will comprise the full analysis set (FAS). Efficacy analyses will be conducted based on the FAS.

For efficacy analyses, the normality of outcome variables will be assessed using the Shapiro–Wilk test. Baseline characteristics will be included as covariates for adjustment in the statistical models. Additionally, comparisons between the robot (intervention) and control groups under each condition will be performed using either the independent t-test or the Mann–Whitney U test, depending on the distribution of the data. To compare post-intervention outcomes between the groups while adjusting for baseline values, analysis of covariance (ANCOVA) will be used. The post-intervention measurement will be the dependent variable, group assignment the independent factor, and the baseline measurement of the outcome will be included as a covariate. This approach accounts for any baseline imbalances and increases statistical power. Assumptions of normality and homogeneity of regression slopes will be assessed prior to analysis. Statistical significance will be set at a two-sided *p*-value of <0.05 for all analyses.

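### A blanket two-sided 0.05 rule covers a secondary list that expands to about 52 to 62 parameters, with no key secondary and no exploratory label

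*Protocol article*

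**What the plan says.** The Outcomes section names one primary outcome: "The primary outcome will be the change in gait speed from T0 to T1", measured by the 10-metre walk test. The Sample size section bases the calculation on that outcome alone.

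The secondary set is introduced by "The secondary outcomes will be the change from T0 to T1 of the following assessments", followed by 12 domains in one undifferentiated list. The same section then describes what several of the instruments record:
- The MDS-UPDRS is described "across four domains: (I) non-motor experiences of daily living, (II) motor experiences of daily living, (III) motor examination, and (IV) motor complications".
- The gait parameters, from an IMU system and GAITRite, "will include stride length, step length, cadence, proportion of single and double support, proportion of swing and stance phases", plus hip, knee and ankle range of motion.
- The dynamometer yields seven measures, and "Measurement will be obtained for both knee flexion and extension at angular velocities" of 60 and 180 degrees per second.
- DEXA yields five measures.

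The Statistical methods section closes with one decision rule: "Statistical significance will be set at a two-sided" p-"value of <0.05 for all analyses". The article gives no order among the secondaries, no key secondary, no multiplicity adjustment and no statement that secondary results are exploratory.

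**The concern.** The sentence on significance is a positive rule. It applies the same threshold to the one outcome on which the trial was sized and to every other comparison. With a long secondary list in 34 participants, some nominally significant differences are to be expected by chance. Under the rule as written, nothing separates them from a confirmatory result.

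What is at stake is the interpretation of the secondary results. The Discussion hopes to clarify effects on gait parameters, including stride length, which is a secondary measure. A chance finding there could be reported with the same standing as the primary result.

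**Working it through.** The article states no endpoint count and no error rate across endpoints, so there is no figure of its own to reproduce. The count below is built from the Outcomes section, on the assumption that each recorded parameter is tested once.

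| Group | Low count | High count |
|---|---|---|
| 4-metre walk, TUG, SPPB, BBS, MDS-UPDRS, FoGQ | 6 (MDS-UPDRS total) | 9 (MDS-UPDRS by four parts) |
| Gait: stride length, step length, cadence, single support, double support, swing, stance, and three joint ranges of motion | 10 | 17 (seven on both systems, plus three ranges of motion) |
| Dynamometer: 7 measures x 2 movements x 2 velocities | 28 | 28 |
| Quadriceps thickness | 1 | 1 |
| DEXA | 5 | 5 |
| MMSE, BDI | 2 | 2 |
| **Total** | **52** | **62** |

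The split between the two gait systems is also an assumption, because the article does not assign parameters to systems. Counting all 10 gait parameters on both systems and splitting the MDS-UPDRS gives 9 + 20 + 28 + 1 + 5 + 2 = 65. Analysing the legs separately for dynamometry and thickness would add 28 + 1 = 29, giving 94. The article does not say that legs are analysed separately.

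**Expected number of false positives with no true effect.** For m tests at two-sided 0.05 the expectation is 0.05m in either direction. Half of that, 0.025m, favours the robot group. Both hold whatever the correlation between tests.

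**Chance of at least one if the tests were independent.** This is 1 - 0.95^m in either direction and 1 - 0.975^m favouring the robot.

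| m | Expected, either direction | Expected, favouring robot | At least one, either direction | At least one, favouring robot |
|---|---|---|---|---|
| 12 (one test per domain) | 0.6 | 0.3 | 46% | 26% |
| 52 | 2.6 | 1.3 | 93% | 73% |
| 62 | 3.1 | 1.55 | 96% | 79% |
| 94 (legs separate, assumed) | 4.7 | 2.35 | 99% | 91% |

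Two features could move these figures. First, the Statistical methods section prescribes both an unadjusted comparison (t-test or Mann-Whitney) and ANCOVA. The count takes one test per parameter, so a second test would add opportunities. Second, allocation is not randomised, so the true rejection rate under no effect may differ from 5%.

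**The case against.** The strongest reply has four parts.

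1. **The top level of the hierarchy exists.** There is one primary outcome and the trial is sized on it. This stands: the secondary tests do not inflate the error rate of the primary conclusion.

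2. **The count is a construction.** The Outcomes section describes what instruments record, not which parameters receive a hypothesis test. Some, such as the dynamometer coefficient of variation, have no obvious direction of benefit, and swing and stance proportions are complementary. This stands in part, which is why the one-test-per-domain figures are shown as a lower bound. However, nothing in the article limits testing to one measure per domain.

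3. **Multiplicity is commonly left to a statistical analysis plan, which is not shown.** This would be a full answer if the article were silent. It is not: it fixes a threshold for every analysis, and a later plan that treated secondaries differently would have to depart from that sentence.

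4. **The Discussion is hedged.** It speaks of the study's findings in general, and gait speed, the primary outcome, is among the effects it names. This stands: the text does not show that the investigators mean to build recommendations on isolated secondary results.

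Two stronger readings are tempting. A reader might infer about three false benefits for the suit, but the test is two-sided, so about three is the total in both directions and roughly half would favour control. A reader might also infer that a false positive is almost certain. That rests on independence, and many of the dynamometer and gait measures are closely related, so the true probability is lower than tabulated. Self-rating by unblinded participants is a separate matter of bias and is no part of this point.

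**Conclusion.** The concern holds for the secondary outcomes only. The article applies one unadjusted threshold to a set that reaches about 52 to 62 parameters when fully expanded. In that case about 2.6 to 3.1 false-positive differences are expected if the suit has no effect, of which about 1.3 to 1.55 favour the robot. These figures assume one test per parameter and a 5% rejection rate under no effect. If testing were confined to one measure per domain, the problem would shrink to 0.6 and 0.3. The article does not say which applies, and its significance rule makes no distinction. This should be corrected, but it does not threaten the primary analysis.

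**What to change.** In the Statistical methods section, replace the wording that extends the threshold to every analysis. State that the two-sided p<0.05 significance claim applies to the primary outcome only. State also that all secondary outcomes are exploratory and will be reported as between-group estimates with 95% confidence intervals and no claim of significance.

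If the investigators want confirmatory secondary claims, they should name a few in advance and control the error rate across them, for example by Holm or fixed-order testing after a significant primary. This step is optional.

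The change takes one paragraph and needs no further participants or measurements. It should be made before any between-group results are seen. The downside is that fewer results can be called significant.

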### Data collection, management, and monitoring

To ensure high data quality, all research investigators and assessors held a series of meetings to discuss and establish standardized assessment protocols. Subsequently, comprehensive training sessions were conducted to ensure that all assessors were thoroughly familiar with the standardized methodologies. Furthermore, we carefully document and distribute standardized research evaluation protocols to facilitate the continuous review of evaluation methodologies and data collection instruments.

All study data will be collected using a standardized electronic Case Report Form (eCRF), and participants will be identified solely by a study-specific serial number. Personal information and collected data will be kept strictly confidential under the supervision of the research PI. Data will be stored in password-protected files within a secure, locked facility. An independent researcher, not involved in the main study activities, will regularly monitor the data. The data management team will develop a data validation plan and will be responsible for query management, coding of adverse events, and reconciliation of serious adverse events.

Regularly scheduled plans for auditing trials are not in place. However, audits may be conducted at any time by an internal auditing organization within the Institutional Review Board (IRB) of Chung-Ang University Hospital, where the clinical trial is being conducted. The audit process will be independent of the investigators and sponsor. Data monitoring committee, consisting of the PI and monitoring agents from the participating hospital, conducts data monitoring every 3 months, with additional irregular monitoring in the event of serious adverse events. The sponsor has played no role in the study’s design and not involved in the collection, analysis, interpretation of data, or writing of the manuscripts.

### Adverse events and harms

Adverse events during this study may include musculoskeletal discomfort, dizziness, fatigue, or general symptoms that could be reported in patients with PD. The most serious expected adverse event is falling. During the exercise intervention, strength training will be conducted in a one-on-one setting with a physical therapist who will continuously monitor for falls. During treadmill training, a safety harness will be used to prevent falls. All adverse events will be monitored. All adverse events that occurred will be reported to PI and ethics committee of the participating hospital within 7 days.

### Ethics and dissemination

Prior to inclusion of participants, we obtained IRB approval for this study (IRB number: 2401–020-587). Informed consent will be obtained from all participants by research investigators prior to their inclusion in the study. The contents of the informed consent form, which were approved by the IRB, include an explanation of the study’s purpose, potential benefits and risks, and provide clear contact information for both the investigator and the IRB in case participants have any questions during the study.

This trial has been registered at Clinical Research Information Service (CRIS) in South Korea (KCT0010793). Any important modifications to the protocol will be promptly communicated to all relevant parties, including research investigators, the ethics committee of the participating hospital, and trial registration, under the responsibility of the PI. Participants will also be informed if the changes directly affect their involvement. The results of this study are expected to be published within 1 year of its completion. The PI and the researcher designated for statistical analysis will have access to the final dataset. Researcher affiliated with HUROTICS Inc. will be prohibited from participating in data analysis. Any data required to support the findings of this study will be available from the corresponding author upon reasonable request.

## Discussion

This study will investigate the effect of a soft wearable robot suit with hip extensor assistance on gait in patients with PD. To the best of our knowledge, this will be the first study to specifically evaluate the impact of hip extensor assistance delivered through a soft wearable robot suit in this population.

We anticipate several advantages that distinguish this study from previous research. First, it will provide evidence on the overall impact of a soft wearable robot suit in patients with PD, including its comfort, usability, safety, and effectiveness in real-world gait training. Second, by focusing specifically on hip extensor assistance, the study will directly address gait deficits characteristic of PD and allow us to clarify its effects on gait parameters such as propulsion, stride length, gait symmetry, and gait speed. By integrating findings from prior studies, the results of this study may also help identify the potential unique benefits of hip extensor assistance compared with other modes, such as flexor-only or combined flexor–extensor assistance. Furthermore, the outcomes of this study may contribute to the development of personalized strategies for promoting gait function in PD patients using wearable robotic devices. Understanding how targeted assistance to a specific joint movement affects gait mechanics will help optimize the design and control algorithms of future devices. Lastly, our findings could provide valuable guidance for future clinical trials and research employing wearable robot suits in gait rehabilitation, ultimately informing evidence-based recommendations for their clinical adoption in PD.
